**Fig. 1 Fig1:**
[figure not shown]
Schematic of the Attention Network Test for Child (Child ANT) adapted from Rueda et al [12]

Each target will be preceded by one of the following four warning cues (asterisk) conditions, as illustrated in Fig. 1: (1) no cue with only the fixation cross displayed; (2) a center cue presented at the location of the fixation cross; (3) a double cue, appearing simultaneously 1 degree above and 1 degree below the fixation cross then the target appears at the level of only one of these two cues; or (4) a spatial cue, appearing 1 degree above or 1 degree below the fixation cross, then the target appears at the location of the cue. Each trial will begin with a fixation period of random duration (400–1600 ms). After that fixation period, the warning cue will be presented for 100 ms and will be followed by another fixation period of 400 ms. subsequently, the target and flankers will appear simultaneously. They will be presented until the child responds. The maximal response time allowed will be 2500 ms. After the response, the target and flankers will disappear, and there will be a last fixation period of 3500 ms minus the response time (RT). Then, the next trial can begin.

To test the influence of mobility on the level of the three components of attention, we will ask the children to complete the experimental task in three random positions: (a) in a fixed seated position corresponding to a posture with very low mobility similar to the demand of sitting in a school environment; (b) standing in an upright position corresponding to the human’s reference posture, requiring real balance control due to the natural body sway; (c) in a free position where the children will be able to move and change their position whenever and as often as they want.

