To check the children’s understanding of ANT, a 12-trial practice block, lasting less than 2 min, will be executed in the seated position. The children will receive feedback on their success. After this practice block, they will execute 48 trials in each position (with a 1-min 30-s break after 24 trials): 4 cue conditions × 2 target locations (up, down) × 2 target directions (left, right) × 3 flanker conditions (neutral, congruent, incongruent). The order of the trials will be randomized. Overall, each experimental block will last less than 3 min. Between each experimental block, the children will have a 3-min break. During these breaks, they will rate the subjective dimension of their arousal based on the adapted Self-Assessment Manikin scale [45]. They will point to one of five figures on a teddy bears’ scale (Fig.2), or between any two figures, which results in a 9-point rating scale. Overall, the experiment will last about 30 min.

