### Statistical analyses

To determine the number of children to include, we relied upon Rueda et al. [12], showing a global sitting performance of an overall RT of 931 ± 42 ms in 6-years-old children born at term and 833 ± 123 ms in 7-years-old children born at term. Because children born prematurely are usually considered to have about a 1-year delay for learning abilities, we calculated that to demonstrate a catch-up related to the mobility condition, sitting being the reference, for each attention component, with an alpha risk of 0.00625 (Bonferroni correction for the number of tests) and a power of 0.80, 24 children would be needed in each group (Power and Precision™ V4, Biostat Inc., Englewood, NJ, USA 2001).

Thus, we will first compare the overall RT of the children born at term versus those born prematurely. Then, we will compare separately the mean scores (± standard deviation) obtained for each of the attention components. After having verified the required assumptions about data distributions (normality of attentional scores, homoscedasticity and sphericity), the level of each attention component will be analyzed by the means of three mixed analyses of variance, with position condition (seated, standing, free) as a within-subject factor and gestational age (children born preterm vs. children born at term) as a between-subject factor. For all analyses, post hoc tests will be conducted using Tukey’s honestly significant difference method when needed.

To evaluate the subjective arousal level of children between the positions, the Friedman test will be performed on each score on the Self-Assessment Manikin scale with position (seated, upright, and free) as a within-subject factor.

The statistical thresholds for significance will be set to 0.05 for the remaining analyses.

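### Practice is given only in the seated reference posture, so position contrasts cannot be separated from posture-specific rehearsal; the likely effect is small and a few warm-up trials per block would largely deal with it

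*Protocol article*

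**What the plan says.** The relevant text is in the protocol article, under Design and setting of the study, Data acquisition and Statistical analyses.

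- **Practice.** The purpose is given as "To check the children’s understanding of ANT". The means is "a 12-trial practice block, lasting less than 2 min, will be executed in the seated position". Feedback is part of it: "The children will receive feedback on their success". No practice standing or in the free position is described.
- **Scored blocks.** After practice, "they will execute 48 trials in each position", with trial order randomised. For the positions, the article says "we will ask the children to complete the experimental task in three random positions".
- **Reference.** The sample-size paragraph aims to "demonstrate a catch-up related to the mobility condition, sitting being the reference".
- **Outcome and analysis.** Alerting, orienting and inhibition are each a difference between two median RTs of correct responses, computed within a position. Each is then analysed by a mixed ANOVA with position as the within-subject factor and birth group as the between-subject factor.

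**The concern.** Every child first handles the head-mounted display, the task and the mouse while seated and receiving feedback. The first attempt at the same task standing, or with freedom to move, falls on trials that count. The run-in is therefore tied to one level of the factor under test, and that level is the reference.

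This differs from the usual order effect. Order effects average out when positions are randomised or balanced, but seated is the rehearsed posture whatever the order. If rehearsal in a posture matters, a seated-versus-standing or seated-versus-free difference could be read as an effect of mobility when part of it is familiarity, and no term in the planned model could tell the two apart. What has to be checked is whether such an effect would reach the scores that are actually analysed.

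**Working it through.** **Inputs from the article.** Practice: 12 trials, seated. Scored: 48 trials per position, three positions. Trial timing: first fixation 400-1600 ms, cue 100 ms, second fixation 400 ms, then the RT and a final fixation of 3500 ms minus the RT. Breaks: 1.5 min within each block, 3 min between blocks. Session: about 30 min. The article gives no figure for a practice or unfamiliarity effect, so every such size below is an assumption.

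**1. The plan's trial count.** 4 cues × 2 locations × 2 directions × 3 flankers = 48, as stated. Each cue median rests on at most 48/4 = 12 trials per position and each flanker median on at most 48/3 = 16, before errors are removed.

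**2. What order can and cannot balance.** There are 6 orders of three positions. With the orders equally weighted, each position is first, second or third equally often.

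| Before the block | Seated | Standing | Free |
|---|---|---|---|
| Earlier trials of any kind, mean of 12, 60 and 108 | 60 | 60 | 60 |
| Earlier trials under that position's instruction, every order | 12 | 0 | 0 |

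General task learning is evened out. Rehearsal in the instructed posture is not, and because it is a fixed function of position, the ANOVA cannot estimate it separately.

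**3. Does a penalty reach the difference scores?** Write a score as median(A) − median(B), both from the same block.

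- *Uniform slowing d on all trials.* (median(A) + d) − (median(B) + d) = median(A) − median(B). It cancels exactly. Overall RT in that position rises by d.
- *Start-up slowing on the first k trials.* Trial order is random, so the expected number of disturbed trials is the same for both members of each pair. With k = 6 (assumed), it is 6 × 12/48 = 1.5 per cue and 6 × 16/48 = 2 per flanker type. The mean score is nearly unchanged and its variance rises. Simulation (assumed trial SD 150 ms, alerting 40 ms, inhibition 80 ms): a 200 ms penalty on the first 6 trials leaves the mean scores at about 40 and 80 ms and raises the SD of a child's score by about 8%. Smaller penalties raise it less.
- *Slowing proportional to RT throughout the block.* The score is multiplied by the same factor. At an assumed 5%, 40 × 1.05 = 42 ms. At 10%, 40 × 1.10 = 44 ms.
- *Slowing that differs by cue or flanker type.* The score shifts by the difference in slowing between the two trial types. The article gives no basis for its size or sign.

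**4. Cost of warm-up trials.** One trial lasts 0.4 to 1.6 + 0.1 + 0.4 + 3.5 = 4.4 to 5.6 s, because the RT drops out. Four trials take at least 4 × 4.4 = 17.6 s and six at most 6 × 5.6 = 33.6 s. At the mid-point of 5.0 s, that is 20-30 s per block.

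The session on these timings has 12 + 144 = 156 trials. At 4.4 to 5.6 s each they take 11.4 to 14.6 min. Adding 3 × 1.5 = 4.5 min of mid-block breaks and 2 × 3 = 6 min between blocks gives about 22 to 25 min. Warm-ups in three blocks add 0.9 to 1.7 min, for about 23 to 27 min.

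**The case against.** The strongest reply is that the asymmetry does not reach the planned analysis. Position enters the planned RT analyses only through the three within-position difference scores. The overall RT comparison is between birth groups, which receive the same practice, and no comparison of accuracy by position is described. The working bears this out: uniform slowing cancels, and early disturbed trials add noise without shifting the mean. This stands, and it limits the point to a minor one.

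Other parts of the reply also stand. The practice is there to check understanding, and understanding carries over between postures. Children in the free position may choose to sit, so that position is not wholly unrehearsed. One comprehension check in one posture contradicts nothing else in the article.

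Three stronger readings are tempting, and the document does not support them.

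- A reader might infer that the standing and free blocks definitely suffer a penalty. No evidence for one, or for its size, is given.
- A reader might infer that early slow trials bias the component scores in an unknown direction. Randomised trial order makes them noise, not bias.
- A reader might take total seated exposure of 12 + 48 = 60 trials against 48 elsewhere as evidence of bias. It is not: earlier exposure of any kind averages 60 trials before each position.

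What the reply does not remove is the tie between rehearsal and the factor being tested. The study's mechanism is mobility raising arousal and so improving alerting. It is conceivable, though not documented, that novelty of the posture also affects arousal and so acts differently by cue type. In that case the score would move, and the design could not distinguish the two explanations. A comprehension check also gives no reason to leave the other two positions without any unscored start.

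**Conclusion.** The concern holds as a small, avoidable asymmetry. Rehearsal in the instructed posture is 12 trials for seated and 0 for standing and free in every order, and neither randomisation nor the mixed ANOVA can separate it from posture. No biased result is demonstrated.

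On the planned scores, a uniform slowing has no effect, and a start-up slowing mainly adds noise to the standing and free scores: about 8% or less in the SD of a child's score, under the assumed trial SD of 150 ms and a 200 ms penalty on 6 trials. Bias in the position contrasts requires a slowing that scales with RT (2-4 ms on an assumed 40 ms score at an assumed 5-10%) or one that differs by cue or flanker type (size unknown). Raw RT or accuracy would be affected directly if compared by position. The term-versus-preterm comparison averaged over positions and the sample size are not affected. This is an inexpensive improvement in precision and interpretability, not a flaw that invalidates the design.

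**What to change.** Keep the 12 seated feedback trials as the comprehension check. Begin every scored block (seated, standing and free alike) with the same small number of unscored warm-up trials, for example 4-6, done in that block's position. State that these trials are excluded from the medians.

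The cost is about 20-30 s per block, which keeps the session within the stated 30 min, and a small change to the E-Prime script and the instructions. The 48 scored trials, the analysis and the sample size stay as they are.

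Two limits should be understood. Warm-ups take the start-up trials in each posture out of scoring, but seated still has the 12 earlier practice trials, so a slowing that lasted through a whole block would remain. Dividing the 12 practice trials into 4 per position would equalise rehearsal at no extra trials. However, 4 trials cannot cover the 4 × 3 = 12 cue-by-flanker combinations in any one posture, so the comprehension check would be weaker. The warm-up option is preferable.

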**Methods:**

This prospective, randomized, controlled trial will focus on psychometric testing of attentional abilities assessed with the Attention Network Test for Child (Child ANT) and involves a mixed measurement design. Forty-eight children aged 7-years, half of whom were premature at birth and in their expected grade without learning difficulties will be included after parental consent. They will be equipped with a head-mounted display in which the Child ANT will be presented. The association of different flankers and pre-cues will allow the measurement of the development level of Alerting, Orienting, and Inhibition function. The task will be composed of one experimental block of trials randomly performed per posture: seated, standing, or free.

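### As written, arousal is rated in the two breaks between three blocks, while the planned Friedman test needs one rating for each of the three positions

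*Protocol article*

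**What the plan says.** The abstract fixes the number of blocks: "The task will be composed of one experimental block of trials randomly performed per posture: seated, standing, or free". The section Design and setting of the study describes the same three positions, taken in random order.

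That section then describes two kinds of break. One lies inside each block: "they will execute 48 trials in each position (with a 1-min 30-s break after 24 trials". The other lies between blocks, and the arousal rating follows directly on it: "Between each experimental block, the children will have a 3-min break. During these breaks, they will rate the subjective dimension of their arousal". No rating after the last block is mentioned. A practice block comes first ("a 12-trial practice block, lasting less than 2 min, will be executed in the seated position"), but it is not one of the experimental blocks.

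For the analysis, the Statistical analyses section says that "the Friedman test will be performed on each score on the Self-Assessment Manikin scale with position (seated, upright, and free) as a within-subject factor".

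**The concern.** The article states both when the rating is taken and which test it feeds, and the two do not fit. A Friedman test on three related conditions ranks the three values within each child, so each child must supply all three. A schedule tied to the breaks between three blocks supplies two.

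The rating matters because the Aim of the study section proposes that freedom of movement helps alerting through higher arousal. The self-rating is the only arousal measure described, and the Friedman test is its only stated analysis. A rating not taken during the session cannot be recovered afterwards, so a team that followed the procedure to the letter would be unable to run the planned test.

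**Working it through.** **Inputs**
- Experimental blocks per child: 3, one per posture, in random order (Abstract, Methods; Design and setting of the study).
- Rating occasion: the 3-min breaks between blocks (Design and setting of the study).
- Levels of the within-subject factor in the Friedman test: 3 (Statistical analyses).
- Children: 2 groups × 24 = 48 (Abstract; Statistical analyses).
- Assumption: a rating made in a break refers to the block just finished.

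The article gives no figure for the number of ratings, so there is none to reproduce. The check is a count.

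**Literal reading: rating in the between-block breaks**
- Breaks between blocks = 3 − 1 = 2, so 2 ratings per child.
- Ratings collected = 48 × 2 = 96. Ratings needed = 48 × 3 = 144. Shortfall = 144 − 96 = 48, one per child.
- There are 3! = 6 possible orders of the positions. In each, the position taken last has no rating, so 0 of 6 orders, and hence 0 of 48 children, give a complete set of three.

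**Which positions are missing**
- Each posture comes last in 2 of the 6 orders and is rated in the other 4. With balanced orders (an assumption; the article says only that order is random), that is 4/6 × 48 = 32 children per posture.
- Any given pair of postures fills the first two places in 2 of the 6 orders: 2/6 × 48 = 16 children per pair.

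**Alternative reading: the mid-block breaks count as well**
- Ratings per child = 3 mid-block + 2 between-block = 5. The first two positions are rated twice and the last once.
- The three mid-block ratings form a complete set at the same point in each position, so 6 of 6 orders and 48 of 48 children could enter a Friedman test. The article would then need to say which of the five ratings is used.

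**With a rating after every block, including the last**
- 3 ratings per child; 6 of 6 orders complete; up to 48 of 48 children and 144 of 144 ratings.

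**Can session length settle the reading?**
- Mean trial length = 1000 ms (midpoint of 400 to 1600) + 100 + 400 + 3500 = 5000 ms. A block takes 48 × 5 = 240 s and practice takes 12 × 5 = 60 s.
- Two 3-min breaks: 60 + 3 × (240 + 90) + 2 × 180 = 1410 s = 23.5 min.
- Three 3-min breaks: 60 + 3 × (240 + 90) + 3 × 180 = 1590 s = 26.5 min.
- Both are loosely compatible with the stated session of about 30 min, so it does not decide the matter.

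**The case against.** The best defence is that the text is loose rather than wrong. It does not say that arousal is rated only between blocks, and it does not exclude a rating after the last one. A test with three positions presupposes three ratings, so one rating after each block is the natural intention, and this is a condensed article. The timings in the same section are also approximate: the trial structure gives about 4 min for 48 trials, while the block is said to last under 3 min. That is a weak basis for exact counting. The mid-block breaks could be meant too, and then every child has a complete set.

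Most of this stands as a limit on the point. A reader might infer that the last position is never rated, that a posture goes unobserved, or that the arousal comparison is lost. The documents do not support these readings as facts. The unrated position differs between children, so no posture goes unrated across the sample. Rank tests for incomplete blocks could still use the two ratings per child, with less information.

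The defence does not remove the mismatch. The nearest thing that the rating sentence can refer to is the 3-min break between blocks. Elsewhere, under Data acquisition, the article ties the observation sheet to every experimental block, so that wording was available for the rating. The mid-block reading still leaves open which rating enters the test. This is also more than a detail left to a fuller document, because the schedule that is stated cannot supply the analysis that is stated.

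**Conclusion.** The point holds as a mismatch between the written rating schedule and the written analysis. On the literal text each child gives two ratings where the Friedman test needs three: 96 of 144 ratings and no complete child among 48. This rests on taking the rating sentence to mean the between-block breaks and on no unstated rating after the last block. If either assumption fails, all 48 children can be complete. Three ratings are probably intended.

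The weight is minor to moderate. Arousal is a supporting measure. The three mixed analyses of variance for alerting, orienting and inhibition rest on reaction times and are unaffected, as is the sample size. It is still worth correcting before data collection, because a missed rating cannot be recovered.

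**What to change.** In Design and setting of the study, replace the rating sentence with wording to this effect: *each child rates arousal at the end of each of the three experimental blocks, including the last, at the same time point after each block.* In Statistical analyses, add that these three ratings, one per position, are the values that enter the Friedman test.

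The cost is one sentence in the procedure, a clause in the analysis, and a few seconds per child for the rating after the last block. Separate Friedman tests by gestational-age group are a matter of choice and not part of this correction.

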**Fig. 2 Fig2:**
[figure not shown]
Teddy bears’ scale adapted from the Self-Assessment Manikin Scale

### Data acquisition

To control for the position instructions, the experiment will be video recorded and an observation sheet completed for each experimental block.

During the Child ANT, the success and RT will be recorded for each trial. According to Fan et al. [10], the level of each attention components in each position will be computed from the RT difference of correct responses between pairs of specific trials. The alerting effect will be evaluated by subtracting the median RT of all double cue conditions for each child from the median RT of the no cue condition across the flanker conditions. The orienting effect will be evaluated by subtracting the median RT of all spatial cue conditions from the median RT of all center cue conditions across the flanker conditions. The inhibition function effect will be evaluated by subtracting the median RT of congruent flanking conditions from the median RT of incongruent flanking conditions across cue conditions.

### Statistical analyses

To determine the number of children to include, we relied upon Rueda et al. [12], showing a global sitting performance of an overall RT of 931 ± 42 ms in 6-years-old children born at term and 833 ± 123 ms in 7-years-old children born at term. Because children born prematurely are usually considered to have about a 1-year delay for learning abilities, we calculated that to demonstrate a catch-up related to the mobility condition, sitting being the reference, for each attention component, with an alpha risk of 0.00625 (Bonferroni correction for the number of tests) and a power of 0.80, 24 children would be needed in each group (Power and Precision™ V4, Biostat Inc., Englewood, NJ, USA 2001).

Thus, we will first compare the overall RT of the children born at term versus those born prematurely. Then, we will compare separately the mean scores (± standard deviation) obtained for each of the attention components. After having verified the required assumptions about data distributions (normality of attentional scores, homoscedasticity and sphericity), the level of each attention component will be analyzed by the means of three mixed analyses of variance, with position condition (seated, standing, free) as a within-subject factor and gestational age (children born preterm vs. children born at term) as a between-subject factor. For all analyses, post hoc tests will be conducted using Tukey’s honestly significant difference method when needed.

To evaluate the subjective arousal level of children between the positions, the Friedman test will be performed on each score on the Self-Assessment Manikin scale with position (seated, upright, and free) as a within-subject factor.

The statistical thresholds for significance will be set to 0.05 for the remaining analyses.

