## Background

Five to 7-years of age is a milestone in children’s development. At this age, they begin school and acquire the basics of fundamental learning such as reading, writing, and calculating. In a general way, these lessons are strongly related to attentional abilities and executive functions such as working memory and inhibitory control in children [1–8].

Since 1990, Posner’s work highlighted three different attentional networks that are thought to relate to the activation of different brain areas [9]. These cerebral networks are related to three components of attention: sustained attention or alerting (maintaining vigilance abilities), selective attention or orienting (ability to shift the attention), and inhibition function (ability to focus on one feature of a stimulus and ignore other interfering features). Fan et al. [10] developed an integrated Attention Network Test (ANT) based on a flanker task [11] in order to independently measure the efficiency of these three networks. This test was validated in adults, where alerting was induced by warning signals given prior to a target event, orienting facilitated by explicit spatial cues prior to a target event, and inhibition function evaluated by introducing incongruent flankers around the target. The adaptation of this test for children born at term at the ages of 4 to 10-years [12] showed an independence in the development of these three attentional systems. Alerting and orienting components may mature at up to 6-years of age then stabilize, while the inhibition function may improve up to the age of 7-years then remain stable after this age [12].

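### The 0.80 power claimed for each attention component rests only on overall seated reaction times; power for the component and position contrasts is unsupported and unknown

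*Protocol article*

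**What the plan says.** The Statistical analyses section bases the sample size on one earlier study of the Child ANT, "showing a global sitting performance of an overall RT of 931 ± 42 ms in 6-years-old children born at term". For the older comparison group it takes from the same study "833 ± 123 ms in 7-years-old children born at term". The link to preterm birth is an assumption: "Because children born prematurely are usually considered to have about a 1-year delay for learning abilities". The gap between 6- and 7-year-olds thus stands in for the gap between preterm and term children at age 7.

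The stated target is "to demonstrate a catch-up related to the mobility condition, sitting being the reference, for each attention component", and the stated result is "for each attention component, with an alpha risk of 0.00625 (Bonferroni correction for the number of tests) and a power of 0.80, 24 children" in each group.

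The same section lists the analyses. The first compares overall RT between term and preterm children. Three mixed analyses of variance follow, one per component, with position (seated, standing, free) within child and gestational group between children. Under Data acquisition, each component score is a difference between two median RTs within a child and a position.

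**The concern.** The inputs and the claim concern different quantities. The inputs describe overall RT, in one position, in two independent groups. The claim concerns a change from sitting in a score that is itself an RT difference. The variance of such a change depends on the component-score SD and on the correlation between positions within a child, and the expected effect is a number of milliseconds of alerting, orienting or inhibition. None of these appears in the paragraph.

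The cost falls on how non-significant results are read. The Aim of the study section predicts that free mobility improves alerting in term children and leaves orienting and inhibition unchanged. Two of the three predictions in that group are therefore nulls. A reader told that each component has 80% power would take non-significance as support for them, and the plan as written does not license that.

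**Working it through.** **Inputs from the document:** means 931 and 833 ms, so the difference is 98 ms; SDs 42 and 123 ms; alpha 0.00625 (= 0.05/8); power 0.80; 24 per group. Sidedness is not stated; two-sided is assumed throughout.

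**1. Reproducing the plan's figure as a two-sample test of overall RT.**
- Root-mean-square SD = √((42² + 123²)/2) = 91.9 ms; standardized difference = 98/91.9 = 1.07.
- Normal formula: n = 2(z₁₋α/₂ + z₀.₈₀)² × 91.9²/98² = 2(2.734 + 0.842)² × 91.9²/98² = 22.5, so 23 per group.
- Noncentral t: noncentrality at 24 per group = 98/√((42² + 123²)/24) = 3.69, power 0.791. At 25 per group it is 0.813, so 25 are needed.

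The stated 24 lies between the two. No component score, position effect or correlation is needed to reach it.

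**2. Sensitivity of that figure to the SD.** With 123 ms in both groups, d = 98/123 = 0.80, power at 24 per group is 0.466, and 43 per group would be needed.

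**3. What the design detects at 80% power** (noncentral t, two-sided alpha 0.00625), in SDs of the change score between two positions:

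| Contrast | Children | Detectable change |
|---|---|---|
| Group by position | 24 vs 24 | 1.08 SD |
| Position, within one group | 24 | 0.80 SD |
| Position, all children | 48 | 0.54 SD |

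Change-score SD = component SD × √(2(1 − ρ)), where ρ is the between-position correlation.

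**4. Illustration in milliseconds.** Component SDs of 50 and 100 ms, ρ = 0.5 and a 30-ms effect are assumptions, not document figures. At ρ = 0.5 the change-score SD equals the component SD.

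| Contrast | Detectable, SD 50 | Detectable, SD 100 | Power for 30 ms, SD 50 | Power for 30 ms, SD 100 |
|---|---|---|---|---|
| Group by position | 54 ms | 108 ms | 0.23 | 0.04 |
| Position, one group | 40 ms | 80 ms | 0.49 | 0.08 |
| Position, all 48 | 27 ms | 54 ms | 0.90 | 0.23 |

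**5. If the overall-RT figures are carried over instead** (98 ms, SD 91.9, ρ assumed), the group-by-position contrast has power 0.41 at ρ = 0, 0.60 at 0.3, 0.79 at 0.5 and 0.97 at 0.7. For half that effect (49 ms, also an assumption) the values are 0.07, 0.11, 0.17 and 0.33.

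Power for the catch-up and position contrasts thus runs from under 10% to over 95%, depending on quantities that the document does not give.

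**The case against.** Several counter-arguments have weight.

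- **Reproducing 24 does not prove what was calculated.** At ρ = 0.5 the change-score SD equals the raw SD, so a 98-ms group-by-position contrast at SD 91.9 also has power 0.79. This stands, but it would still be a calculation on the overall-RT scale, with no component effect or SD behind it.
- **A reader might infer that no position or catch-up test reaches 80%, or that power is probably far lower.** The document does not support that. The position contrast over all 48 children reaches 0.90 in one of the cases above, and the interaction reaches 0.97 in another.
- **The catch-up need not mean an interaction.** It can equally mean a change from sitting within the preterm group. This stands, which is why all three contrasts are shown.
- **A reader might infer that there is no alerting or orienting deficit to catch up on,** since the Background says "Alerting and orienting components may mature at up to 6-years of age then stabilize". That sentence is hedged and concerns term-born children. The Background also says that preterm children may reach the adult level of orienting at 8 years, and it reports a delay of about one year. Only for alerting does it cite no preterm difference, at about 8 years. The argument is partial at best.
- **A reader might infer that entry criteria remove the assumed delay,** because children are to be "in their expected grade without learning difficulties will be included after parental consent" (Abstract, Methods). That is plausible, but nothing in the document sizes its effect on RT.
- **The alpha for each contrast is not certain.** The section uses 0.05 for remaining analyses and Tukey post hoc tests. The 0.00625 used here is the level that the plan ties to its power claim.
- **The article condenses a fuller protocol.** Component inputs might exist there. The article nevertheless makes a specific claim and shows its inputs, and those inputs do not support it.

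**Conclusion.** The point holds in limited form: the sample-size statement is wrong as written. The inputs support about 79% power, at two-sided alpha 0.00625, for a 98-ms difference in overall RT between groups with SDs of 42 and 123 ms. That matches the first planned analysis, and it falls to 47% if both SDs are 123. It also rests on 6-year-old term-born children as a proxy for preterm 7-year-olds; no preterm data enter.

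For the component scores and position contrasts, 0.80 is unsupported and the true power is unknown. The document does not establish that it is low, and it gives no basis for saying that it is adequate. The standardized detectable effects rest only on the group sizes, the alpha, two-sided t tests and complete data. The millisecond figures rest also on the assumed SDs and correlation.

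**What to change.** Rewrite the sample-size paragraph:

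1. Say that 24 per group gives about 79% power at two-sided alpha 0.00625 for a 98-ms difference in overall seated RT with SDs of 42 and 123 ms, and about 47% if both SDs are 123.
2. Delete the claim of 0.80 power for each component.
3. State what the design detects at 80% power and the same alpha: about 1.08 change-score SD for group by position, 0.80 SD for a position contrast within one group of 24, and 0.54 SD over all 48 children. Translate these into milliseconds over declared ranges of component SD and between-position correlation, labelled as assumptions. If component-score data are available to the authors, use them instead.
4. Report component results with confidence intervals, so that non-significance is not read as an 80%-powered null.

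The mixed analyses of variance can stay as planned, and the component tests need not be demoted to estimation. The cost is one paragraph and a less favourable stated figure; no extra children are needed.
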